## Abstract

**Introduction:**

Psychosocial dysfunction is associated with poor longitudinal course of depression and is not sufficiently addressed by existing pharmaceutical or psychological treatments. The aim of the current study is to evaluate the efficacy of a novel intervention designed to improve psychosocial function in depressed individuals. Impaired cognition, emotion processing, and social cognition appear to underlie (i.e., cause) psychosocial dysfunction in depression. The current treatment will target functioning in these domains (i.e., cognition, emotion, social cognition) with repeated training tasks, following the rationale that therapeutic benefits will arise in psychosocial functioning. It is expected that personalizing treatment by participants’ baseline functioning will enhance clinical efficacy, by comparison with standard treatment in which baseline functioning is not considered.

**Methods:**

The study is a randomized, controlled treatment (RCT), in which the efficacy of a personalized and standard intervention will be compared. Sixteen treatment sessions will be administered over an 8-week period. These treatments are designed to improve cognition, emotion processing and social cognition. Assessments of psychosocial functioning, as well as a number of secondary outcomes, will occur at baseline, 4 weeks (mid-RCT), 8 weeks (end of RCT), and in the observational period at baseline (week 9) and 3 and 6 months post-RCT. Recruitment will commence in July 2017, including subjects diagnosed with major depressive disorder according to DSM-IV-TR criteria.

**Discussion:**

This research will provide new insight into the roles of cognition, emotion processing, and social cognition in psychosocial dysfunction in depression. In addition, the relative clinical efficacy of personalized versus standard treatment approaches will be assessed.

**Ethics and dissemination:**

This study has been approved by the human research ethics committees of the Royal Adelaide Hospital and the University of Adelaide (ethics code: R20170611). The study has been registered with the Australia and New Zealand Clinical Trials Registry Registration number: ACTRN12617000899347, web link: http://www.anzctr.org.au/Trial/Registration/TrialReview.aspx?ACTRN=12617000899347p. The results of the current study will be published in academic journals following completion of recruitment in 2019. Data will be owned and retained by the University of Adelaide, with access restricted to the research team responsible for the study.

## Introduction

Depression is the leading cause of mental illness worldwide, affecting approximately 322 million individuals (1). The illness is characterized by prolonged negative mood, anhedonia, and impaired cognition. Depressed individuals also demonstrate significantly impaired psychosocial function, indicated by diminished organizational, occupational, and social ability (2, 3). In addition to the substantial burden of depression on the daily lives of individuals (4) depression impacts on a societal level by reducing occupational productivity (5, 6). Established therapies (e.g., psychotherapy, CBT) and pharmaceutical treatments are costly and lead to high rates of recurrence in the long term (6). As a consequence, there is a clear need to develop alternative and/or complimentary treatments for depression.

It is possible that existing treatments for depression underperform because they do not sufficiently address psychosocial functioning (2, 7). Psychosocial function can be defined on a micro level as our day-to-day ability to contend with environmental and social tasks (e.g., maintaining work and relationships), and on a macro level as the pursuit of significant life outcomes (e.g., self-actualization) (7). Previous work has operationalized these dimensions, such that quantitative and psychometrically valid assessments of psychosocial impairment have been established (7–9). Psychosocial functioning appears to be related to a number of other functional outcomes (e.g., positive future outlook, ability to derive pleasure from life events), suggesting that psychosocial function contributes to mental health in general (10, 11). Psychosocial dysfunction is prevalent in depressed individuals and does not appear to improve even in patients who are symptomatically recovered (3). Ongoing psychosocial dysfunction may lead to recurrent episodes of depression, as impaired functioning negatively interacts with cognitive and emotional vulnerability in previously depressed individuals (2, 12–14).

Existing evidence indicates that cognitive, emotional, and social cognitive factors underlie deficits in psychosocial functioning (11, 13–16). The proposed study follows this model, stipulating that improvements in cognition, emotion, and social cognition should flow on to psychosocial functioning. Given the importance of this model in the current study, the relationship between the three underlying domains and psychosocial functioning will be explored.

### Cognitive Impairment

According to DSM-5 criteria the cognitive symptoms of major depressive disorder (MDD) are impaired decision making, management of attention, and coordination and maintenance of information in working memory (17). Research has also identified deficits in verbal ability (18), visuospatial processing (19), and psychomotor speed (19). The finding that cognitive deficits occur across multiple domains suggests that depression interferes with underlying cognitive faculties, and with the coordination of cognitive subsystems, rather than interfering a specific modality of cognition. Our cognitive abilities are crucial to daily functioning, and to the severity of several cognitive difficulties associated with depression (e.g., hyper-sensitivity to negative feedback). Cognitive treatments target improvement of cold cognition, with the rationale that increasing functioning will benefit performance in hot cognitive tasks, and hence improve experience of everyday life, psychosocial functioning, and day-to-day functioning. In addition, cognitive impairments may mutually interact with emotional and social factors to maintain or exacerbate depression, or lead to recurrent episodes (14, 16).

Psychosocial and cognitive impairments in depression and in other illnesses are associated with elevated levels of several inflammatory cytokines (20, 21). Research by the [name] group (22, 23) demonstrated that IL-8, IL-1beta, and tumor necrosis factor (TNF) are associated with memory, processing speed and motor function in the elderly. In addition, inflammatory C-reactive protein (CRP) may also be associated with depression symptoms (24), and the neurotransmitters 5HT, DA, and NE appear to be related to psychological stress (25). Investigating biomarkers for psychosocial functioning and cognitive dysfunction presents a valuable area for research, as there is potential for developing objective measurements of dysfunction predisposition, for improving our understanding of the neurological mechanisms of depression and associated poor psychosocial functioning (e.g., neurotrophic theory), and for improving pharmacological treatments that address not only symptoms of depression but also psychosocial functioning and workplace functioning.

A large body of work has investigated the selective treatment of impaired cognition in depression with cognitive remediation programs (2, 5, 26), which typically involve repeated completion of cognitive tasks over several weeks. The results of such programs generally reveal that patients improve on measures of executive, visuospatial, and verbal function (2). These results support the theory that repeated activation of brain regions *via* cognitive treatment increases neuroplasticity and improves neural function (27). Although cognitive gains following remediation programs are relatively consistent, the transfer of this benefit to occupational function, resilience, and psychosocial functioning are not well established (15). It is possible that transfer of cognitive skills does not reliably occur because remediation programs do not also address impaired social cognitive skills and emotional processing, which may negatively interact with cognition on depression outcomes. The following paragraphs discuss the role of emotion processing and social cognition in MDD, and highlight how an integrated and personalized treatment approach may be critical to maximizing treatment outcomes.

### Emotion Processing

Our experience of emotion is fundamentally linked to cognition. Evidence for this link is demonstrated at a neurological level by overlap in activation patterns of cognitive processes and emotional experience (28–30). The phenomenological parallels of emotion and cognition are consistent with cognitive models of depression (31), which stipulate that interplay between cognitive vulnerability and negative emotion both lead to and sustain MDD. Specifically, cognitive models stipulate that attention and memory systems are biased to focus on negative information, suppress adaptive coping strategies (e.g., flexibility), and encourage maladaptive strategies (e.g., rumination) (32). The critical importance of emotion processing in coping and information processing supports the importance of this factor in determining overall psychosocial functioning (15).

The close overlap between emotion and cognition suggests that cognitive remediation should not neglect the role of emotion in treatment programs (33). Previous work in cognitive–emotional treatment has shown promising results in the implementation of working memory tasks with valenced stimuli (34, 35). Iacoviello et al. (35) conducted a study comparing the benefit of an integrated cognitive–emotional treatment task with that of a pure cold cognitive treatment task for subjects with MDD. The results showed that the integrated cognitive-emotional training resulted in greater reduction in depression symptoms and negative self-referential biases. By contrast, both the cold cognition and integrated tasks resulted in similar gains in attention and working memory performance. These findings are consistent with the notion that cognition and emotion are closely linked, and imply that an integrated treatment approach may result in broader transfer of therapeutic benefit.

Recent work by Wu et al. (36) suggests that dysfunctional emotion processing may play a crucial role in the development and maintenance of geriatric depression. The authors evaluated the positive effect of reminiscence therapy, in which older female patients with depression symptoms verbally recounted earlier life experiences by viewing pictures of past events. A clinical nurse encouraged the patient to recount these memories from different perspectives, and highlighted positive comparisons with the patients’ current lives. Posttreatment anxiety and depression symptoms were reduced, suggesting that encouraging flexible and positive retrieval of episodic memory may attenuate negative emotion processing. It is possible that emotional dysregulation may play a greater role in geriatric depression than in standard MDD, as the elderly often lack sufficient social support and experience rapid physiological decline (36). Taken together, these findings suggest that older subjects in the current treatment may benefit from emotion processing training tasks focused on redressing negative social biases and negative self-evaluations.

### Social Cognition

Social cognition refers to the perception, identification, and interpretation of social information in interpersonal interaction (16). Maintaining function in this domain involves incorporating information from a range of social cues including prosody, facial expression, body language, verbal content, and theory of mind. Research has identified that social cognition may be impaired in individuals with depression, though the social cognitive deficit is less severe than in other psychiatric illnesses (e.g., schizophrenia) (37, 38). However, social cognition deficits in depression should not be overlooked, as issues with social interaction are associated with suicidality (39), and with severity of depression symptoms (40, 41).

Given the complexity of social interactions, it stands to reason that cognitive functions (e.g., attention, processing speed) are crucial in maintaining fluid and adaptive social ability. Likewise, emotional recognition and bias play an important role in identification and perception of social information. Impaired emotion recognition may cause incorrect or biased assessment of social interaction, which may exacerbate depressed mood and lead to further negative social interactions (16). In turn, negative social experiences may lead to subsequent avoidance of interpersonal interactions, further enhancing feelings of isolation and impaired mood. The interplay between social cognition, emotion, and general cognition further highlights the need for an integrated treatment approach. In addition, the broad and inter-related deficits associated with social cognitive issues suggest this factor contributes substantially to psychosocial functioning. This being said, the link between social cognition and psychosocial functioning has only recently been empirically investigated (16), and pilot data from our group suggest this relationship; supporting the need for the current research.

Social cognition is typically evaluated by one’s ability to read facial emotions (42). Depressed persons are typically impaired in facial affect recognition, in part due to a tendency to negatively interpret facial emotions (43). A plausible explanation is that impaired attention and emotional interpretation may cause depressed individuals to focus on mood-congruent (i.e., negative) features of facial affect. Other studies of social cognition employ videos of social interactions, which are intended to be more naturalistic and contain more dynamic social features (i.e., body language, prosody, verbal information) (44, 45). These tasks emphasize theory of mind, as reliance on syntactic and visual information alone is insufficient to detect nuanced social interactions (e.g., sarcasm). Social cognition can also be measured with prosody tasks, in which several syntactically identical sentences are presented with different emotional intonations.

The current treatment will use an integrated approach in which cognitive remediation and cognitive training techniques are employed with cognitive, emotional, and social cognitive stimuli. While traditional cognitive training has been shown to increase psychosocial functioning (46, 47), it is expected that the addition of emotional and social training domains will extend and enhance this effect. Similar techniques have been employed to address emotional and social impairment in other psychiatric illnesses, including bipolar (48) and schizophrenia (49). The results of these studies suggest that social and emotional training may provide benefits in domains of daily life (e.g., occupational functioning). The clinical efficacy of these strategies in treating major depression has not yet been evaluated and is hence a primary interest of the current study. It is expected conducting remediation and training in three domains (i.e., cognition, emotion processing, and social cognition) will improve psychosocial functioning to greater extent than is achieved by treating cognition alone.

### Personalization

Given the multifaceted nature of impairment in depression, it is reasonable to assume that deficits will not occur in a uniform nature within individuals. Certain individuals may be disadvantaged specifically in domains of emotional processing, while others are more disadvantaged in terms of cold cognitive ability or social cognition. Previous interventions may not have led to consistent improvements in psychosocial functioning because individual differences in domain-specific impairment were not addressed. In fact, existing interventions assume that group means (i.e., norms) reflect impairment at an individual level, and hence that a generalized treatment approach is sufficient. Given the heterogeneity of impairment observed between individuals with MDD (12), it is possible that a standard treatment approach is not optimal (50). In particular, standard treatment approaches may misappropriate resources and time to clinical domains which are not relevant or helpful to the individual. In contrast, personalized approaches tailor treatment by targeting baseline deficits within individuals, enabling treatment to focus on impaired domains, while also spending less time addressing more functional domains. Personalization may improve treatment efficiency and efficacy, in contrast to the traditional standard approach.

The current investigation will evaluate the personalized approach, by comparing psychosocial functioning following a personalized intervention and a standard (i.e., non-personalized) intervention. The personalized intervention will tailor treatment tasks around baseline individual deficits, such that the individual’s most impaired domains receive the greatest attention. Given the importance of cognition, emotion processing, and social cognition in determining psychosocial functioning, the CERT-D treatment will be tailored by patterns of impairment observed in these three domains. For example, a participant who demonstrates severe cognitive impairment will receive a greater number of treatment sessions devoted to cognition, with fewer sessions devoted to emotion processing and social cognition. Overall, it expected that both personalized and standard treatments will result in improved psychosocial functioning, which is expected to be retained over a 6-month observational period. However, it is predicted that the clinical effect on psychosocial function will be greater following personalized, relative to standard, treatment.

In summary, the cognitive and emotional recovery training program for depression (CERT-D) study will evaluate a novel treatment for depression, employing an integrated cognitive, emotional and social cognitive approach. The primary outcome will be change in psychosocial function over the intervention and subsequent observational period. Performance in several secondary domains will also be evaluated, including depression symptom severity, resilience, occupational functioning, cognitive failures, and functional disability. In addition, the study will examine biomarkers of cognitive and psychosocial dysfunction in depression, providing an opportunity to expand our knowledge of this domain. This research will advance the field by evaluating the efficacy of integrating training of cold cognition with emotion processing and social cognition. The integrated approach contrasts with traditional cognitive remediation, which has primarily focused on the improvement and application of executive training. In addition, the current methods allow evaluation of the relative clinical efficacy of personalized and standard treatment approaches in remediating psychosocial dysfunction in MDD.

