## Methods

### Objectives

The primary objective of the CERT-D is to evaluate whether treating cognition, emotion processing, and social cognition leads to immediate and longitudinal benefit in psychosocial functioning. To achieve this objective, participants will complete either a personalized or standard (non-personalized) treatment devoted to increasing performance in these domains. Participants in the personalized group will receive a tailored treatment incorporating a greater number of sessions devoted to their domain(s) of primary baseline dysfunction. By contrast, the standard treatment group will complete a pre-established battery of treatment independent of baseline deficits.

The key hypotheses and aims of the current study are as follows:
*Hypothesis 1*:Overall, psychosocial functioning will be improved at 8 weeks [end of randomized, controlled treatment (RCT)] relative to baseline. Psychosocial functioning in the observational period (post-RCT) will not decline at 3 and 6 months relative to post-RCT baseline.*Related Aim*:To evaluate which subdomains of psychosocial function (e.g., autonomy, social relationships) are sensitive to change over time from the CERT-D.*Hypothesis 2*:Performance in secondary outcome measures will improve at 8 weeks relative to baseline, and will be retained over a 6-month observational period. Secondary outcomes include occupational functioning, cognitive failures, functional disability, resilience, and depression symptom severity.*Hypothesis 3*:It is expected that the personalized treatment group will display greater psychosocial improvement at 8 weeks (compared to baseline) than subjects who complete a standard treatment.*Hypothesis 4*:Biological and genomic signatures will be associated with psychosocial functioning, as well as cognitive, emotional, and social cognitive performance.

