### Study Design and Recruitment

The CERT-D study will commence in July 2017. The study will be a RCT, comparing the clinical efficacy of a personalized and standard intervention. Psychosocial functioning is considered the primary outcome. An effect size of approximately *d* = 0.5 is expected with regards to change in psychosocial function over the intervention. Given the intended sample size of 100, the study will achieve statistical power of 89% (1 − β = 89). The rationale for this “medium” effect size is that previous interventions have found positive outcomes approximate to this magnitude (5, 35), for example in cognitive functioning.

The trial will include 16 treatment sessions designed to improve cognition, emotion processing, and social cognition administered over an 8-week period. Assessments will occur at baseline, 4 weeks (mid-RCT), 8 weeks (end of RCT), and in the observational period at baseline (week 9) and 3 and 6 months post-RCT (see Figure 1). Assessments will measure psychosocial functioning, cognition, emotional state, social cognition, as well as occupational functioning, depression symptom severity, functional disability, cognitive failures, and resilience. Three assessment visits will also include taking blood for biomarker and genetic analysis. Recruitment will include individuals between the ages of 18 and 75, who will be invited to participate *via* research clinics of the Department of Psychiatry, University of Adelaide, and within the Central Health Network in Adelaide, South Australia. It could be argued that the age range should be restricted to younger adults (<60), such that subjects with geriatric depression are excluded. However, recent work has suggested that cognitive training strategies are efficacious in the treatment of geriatric depression (47, 51, 52). Given the current intervention shares many components of traditional cognitive training, it is suggested that the CERT-D intervention should benefit older (i.e., 60–75 years) patients.

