## Intervention Outcomes, Analyses, and Dissemination

The primary outcome of the CERT-D will be psychosocial functioning. Specifically, it is expected that psychosocial functioning will improve at 8 weeks (end of RCT) relative to baseline. Post-RCT psychosocial functioning is expected to be maintained over the 6 months observational period. Performance in secondary outcome measures is expected to demonstrate a similar effect of treatment. Secondary outcomes include depression symptom severity, occupational functioning, resilience, functional disability, and perceived cognitive failures. In addition, the personalized treatment group is expected to show greater improvement over time relative to the standard treatment group. Finally, the association between biomarkers and psychosocial and cognitive performance before and following treatment will be evaluated.

Statistical analyses will be performed with a mixed model ANOVA with time (baseline, 8 weeks, baseline post-RCT, 3 months post-RCT, 6 months post-RCT) and treatment type (personalized, standard) as independent variables. Psychosocial functioning (FAST score) will be the dependent variable. It is expected that overall psychosocial functioning will improve at post-treatment relative to baseline, and that this improvement will be greater in the personalized treatment arm relative to the standard treatment arm. Biomarker analyses require specifically tailored software and will ultimately be entered into simple and stepwise linear regression analyses. These analyses will determine whether individual biomarkers (e.g., CRP), or combinations of biomarkers, are related to cognition (i.e., THINC-it performance) or psychosocial functioning.

Within the personalized treatment group, further analyses will evaluate whether there are any differences in psychosocial functioning owing to the domain-specific treatment groups. That is, will there be any differences in post-RCT psychosocial functioning between the high cognition, high emotion, and high social cognition treatment groups? Given the novelty of the current treatments, these analyses will be exploratory. As with the primary outcome, analyses for this outcome will be conducted with mixed model ANOVAs.

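### The primary outcome is not held to one time window, and no single between-arm comparison is named as the one that decides the trial

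*Protocol article*

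**What the plan says.** The window of the primary outcome appears in several places in the protocol article.

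- **Introduction, Personalization (closing summary):** "The primary outcome will be change in psychosocial function over the intervention and subsequent observational period". That is 8 weeks plus 6 months, about 34 weeks.
- **Objectives, primary objective:** whether the treatment "leads to immediate and longitudinal benefit in psychosocial functioning".
- **Objectives, Hypothesis 1 (arms pooled):** improvement at 8 weeks, and then "Psychosocial functioning in the observational period (post-RCT) will not decline at 3 and 6 months relative to post-RCT baseline".
- **Objectives, Hypothesis 3 (arms compared):** "the personalized treatment group will display greater psychosocial improvement at 8 weeks (compared to baseline) than subjects who complete a standard treatment". It has no follow-up component.
- **Study Design and Recruitment:** "Psychosocial functioning is considered the primary outcome", with no time point. The effect size of about 0.5, with 89% power at a sample of 100, is for "change in psychosocial function over the intervention". The intervention lasts 8 weeks.
- **Intervention Outcomes, Analyses, and Dissemination:** "Specifically, it is expected that psychosocial functioning will improve at 8 weeks (end of RCT) relative to baseline". The next sentence expects the gain to be maintained over the 6-month observational period. The personalized arm is then expected to improve more over time, with no visit named. FAST is analysed in a mixed-model ANOVA with two treatment types and five time levels (baseline, 8 weeks, week 9, and 3 and 6 months post-RCT).

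**The concern.** A randomized trial needs one between-arm comparison, fixed in advance, that settles its main question. Here the outcome and the objective run to 6 months after treatment, the randomized hypothesis stops at 8 weeks, and the analysis section names a model but no contrast. The Introduction's primary outcome, taken over its full window, has no numbered between-arm hypothesis and no power statement.

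An arm difference that is clear at week 8 but gone by 6 months would support Hypothesis 3. A difference seen only at follow-up, or only in the omnibus arm-by-time test, could be presented under the Introduction's definition or the analysis section's wording. In each case the authors could cite the protocol for calling the result primary. What is at stake is whether a reader of the results can tell which comparison was meant to decide the trial before the data were seen.

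**Working it through.** **1. The windows side by side**

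| Place | Window | Arms compared? |
|---|---|---|
| Introduction summary | Intervention plus observational period | Not stated |
| Primary objective | Immediate and longitudinal | Not stated |
| Hypothesis 1 | 8 weeks, then no decline at 3 and 6 months | No, pooled |
| Hypothesis 3 | 8 weeks versus baseline | Yes |
| Effect size and power | Over the intervention | Not stated |
| Analysis section, primary expectation | 8 weeks, with maintenance in a separate sentence | No |
| Analysis section, arm expectation and ANOVA | Over time, five levels | Yes, no contrast named |

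The long and the short window both appear in the operative sections, and the row for the planned model does not choose between them.

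**2. The stated power.** Inputs from Study Design and Recruitment: d = 0.5, N = 100, power 89%. Allocation ratio, alpha and sidedness are not given; I assume 1:1 (50 per arm) and two-sided 0.05.

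- Arm difference in 8-week change, d standardized on change: noncentrality = d × √(n/2) = 0.5 × √25 = 2.5. Power = Φ(2.5 − 1.96) = Φ(0.54) = 70.5%; by noncentral t, 69.7%.
- The same, one-sided 0.05: 80.4% (t: 79.9%).
- Within-subject change, all 100 pooled, paired t: 99.9%.
- Within-subject change in one arm of 50, paired t: 93.4%.

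None of these gives 89%. It can be reached only with inputs the protocol does not state, for example a one-sided alpha of 0.10 (88.6%), or d on the raw-score SD with an assumed baseline to 8-week correlation of 0.7 (89.2%).

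**3. What 89% would need for the 8-week arm difference.** n per arm = 2 × (1.960 + 1.227)² / 0.5² = 81.2, so 82 per arm and 164 in total. At 50 per arm, the smallest d giving 89% is (1.960 + 1.227) × √(2/50) = 0.64.

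**4. The choice of window changes the power.** Suppose the arm difference is d = 0.5 at all four post-baseline visits in the model and the deciding quantity is their mean. With an assumed common correlation ρ between change scores, noncentrality = 2.5 / √((1 + 3ρ)/4):

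- ρ = 0.5: 2.5 / √0.625 = 3.16, power about 89%.
- ρ = 0.8: 2.5 / √0.85 = 2.71, power about 77%.

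The match with 89% at ρ = 0.5 rests on a correlation the protocol does not give, so it does not show how the figure was obtained.

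**5. How often the windows would disagree (illustration).** With 50 per arm, two-sided 0.05, a true d = 0.5 at every visit and ρ from 0.5 to 0.8, simulation gives opposite verdicts from the 8-week and 6-month contrasts in 18% to 29% of trials. If the difference fades to d = 0.25 at 6 months, they differ in 47% to 51%.

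**The case against.** The strongest reply is that the Introduction sentence is not out of line with the rest. It agrees with the primary objective, with Hypothesis 1 and with the maintenance sentence in the analysis section. It names a variable and a follow-up period, sets no success rule and requires no arm difference; the same paragraph raises the arm comparison separately. Hypothesis 3 does fix a time point for that comparison. Contrasts are also often left to an analysis plan, which is not shown here. All of this is fair. It means the fault cannot be placed on one stray sentence.

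It also rules out two stronger readings. A reader might infer that an arm difference lost by 6 months would fail the Introduction's outcome, so that one data set is both a success and a failure. That requires a between-arm criterion the sentence does not contain. A reader might also infer an inflated false-claim rate. Three tests (week 8, 3 months, 6 months), each at two-sided 5%, give 13.1% to 10.9% for at least one significant result at assumed correlations of 0.4 to 0.7. That holds only if a difference at any one visit were accepted, and the protocol states no such rule. A joint rule, with significance in the same direction at week 8 and at 6 months, would give about 0.7% to 1.7%, below 5%. The direction of the error depends on the rule supplied.

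What remains is that the document itself states both windows, and its analysis section drops the time point that Hypothesis 3 had fixed. An analysis plan would have to choose between them rather than merely add detail.

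**Conclusion.** The concern holds as a looseness in the primary outcome. The outcome statement and the primary objective span the intervention and the 6-month observational period, the randomized hypothesis is at 8 weeks, the effect size is for the intervention, and the planned ANOVA has no deciding contrast. This conclusion rests on the text alone.

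The size that can be given is the power for the comparison the randomization supports most directly: about 70% at N = 100 for d = 0.5 between arms on 8-week change, against the stated 89%. It assumes 1:1 allocation and two-sided 5%. The protocol does not say whether its d is between arms or within subjects, so this shows that 89% cannot be carried over to Hypothesis 3 on those assumptions. It does not show which calculation was intended. The disagreement rates and the 11% to 13% any-visit figure are illustrations under assumed correlations and, for the latter, an assumed rule; neither is an operating characteristic of the plan.

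**What to change.** - **Introduction summary and analysis section:** state that the single primary between-arm comparison is the difference in FAST change from baseline to week 8 (Hypothesis 3), tested as that named contrast from the model.
- **Follow-up:** label arm differences at 3 and 6 months as secondary. Keep the pooled no-decline statement of Hypothesis 1 as a secondary maintenance outcome.
- **Objectives:** reword the primary objective to match.
- **Study Design and Recruitment:** tie the power statement to this contrast, giving allocation ratio, alpha, sidedness and whether d is on change or raw scores. On the assumptions above, report about 70% for N = 100.

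No visits or measurements are added, but this is more than an edit of one sentence. Longitudinal benefit moves from the primary objective to a secondary claim, and the stated power becomes less favourable. Keeping 89% for this contrast at d = 0.5 would take 164 participants.
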